### Assessments

The primary outcome is agoraphobic avoidance assessed by the O-AS.^8^

The secondary outcomes are: agoraphobic distress (O-AS)^8^; paranoia (Revised Green *et al* Paranoid Thoughts Scale)^9^; number of social contacts (Social Contact Assessment).^10^

Treatment acceptability will be measured postintervention by the Theoretical Framework of Acceptability questionnaire^11^ and side effects by the Oxford—VR Side Effects Checklist.^6^ These data are only collected after people receive gameChange VR therapy. These assessments will be administered via an electronic link (or paper copy) provided by the treatment deliverer.

Basic sociodemographic and clinical information will be collected for all participants (age, gender, ethnicity, main language, clinical diagnosis, socioeconomic status, psychiatric medication).

The health economic evaluation will use the: EQ-5D five-level (5L),^12^ 20-item Recovering Quality of Life (ReQol-20)^13^ and adapted version of the Client Service Receipt Inventory (CSRI).^7 14^

### The psychological intervention: gameChange VR

The treatment being tested is gameChange, which is UKCA/CE marked and Digital Technology Assessment Criteria approval is in place. It has NICE EVA approval for use in the NHS with patients with psychosis experiencing severe agoraphobic avoidance. The gameChange software application is composed of a set of virtual environments, including different scenes created using 3D models, ambient audio and 3D virtual characters, with animations and speech. The environments are driven by source code which handles the logic of the programme, the behaviour of the computer characters, as well as the user interaction and data storage. gameChange is certified as a VR application for adults (age ≥16 years) who are anxious about everyday situations because of agoraphobic-type fears and it is intended to reduce anxiety around other people. The software was programmed by Oxford VR/RealisedCare. The software is built using Unity (Unity Technologies). Unity acts as a render engine, displaying the virtual environments to the user through the headset. The application runs through the Unity software application on a Meta Quest 3S VR Headset. The programme is free-standing (ie, not dependent on NHS IT infrastructure and it does not connect with NHS electronic records) and simply runs on the headset.

The staff member in the first session can help show the person how to put on the headset and run the application. Detailed guidance on use is included within the application. Participants have a short tutorial showing them how to interact with the virtual environment and advising them of safety precautions. The application is supported by a staff member, who will be present for at least the first session but up to approximately six sessions (depending on patient preference). Additional sessions can be conducted remotely, especially if a participant has taken a headset home. The treatment is designed to be delivered in approximately six sessions, each involving 30 min in VR. It can be supported by a variety of mental health workers—the choice in each site will be made according to how it would be implemented in day-to-day practice. The staff member encourages the person to apply the learning from VR in the real world via helping set homework tasks to be carried out between sessions. The O-AS is also used by the staff member at meetings to monitor progress (and may be used later in research publications eg,to discover trajectories of change). The staff deliverer may also use the Oxford Cognitions and Defences Questionnaire to help guide treatment.^15^

gameChange is a cognitive treatment that aims for patients to relearn safety by testing their fear expectations. Within the VR environments, a virtual coach guides the person through the treatment. When first entering VR, the patient goes into the coach’s virtual office and is guided in how to use VR. At the beginning of the first session, the virtual coach explains the rationale behind the treatment, and the participant selects one of the six VR scenarios. The six VR scenarios are a: café, GP waiting room, pub, bus, street scene and newsagent. Each scenario has five degrees of difficulty (eg, the number and proximity of people in the social situation increases) and participants work their way through each level of difficulty. There are game type tasks within a number of the levels. A participant can choose a different scenario in each session or repeat a previous situation. gameChange is now delivered on standalone headsets. Headsets can be left with patients during the provision of the therapy, meaning that staff contact time could be lower and can also be largely done remotely. Patients may be encouraged to use the VR at home for 20–30 min at times that are most helpful for them.

### Control condition

Participants who are allocated to the waitlist control arm will continue to receive their usual care (TAU). TAU for the participants within this trial will typically consist of prescription of psychiatric medications and meetings with a mental health practitioner. TAU will vary across individuals. We will collect detailed data on TAU. After the 26-week assessment, gameChange will be provided to individuals in the control arm.

### Serious adverse events

SAEs are recorded using an SAE report form. Each participant’s medical notes will be systematically checked for SAEs following completion of the final assessment to ensure all SAEs are recorded. We will also record any SAEs that come to the attention of the assessor or gameChange deliverer. An adverse event is defined by the ISO14155:2011 guidelines for medical device trials as serious if it: (A) results in death, (B) is a life-threatening illness or injury, (C) requires hospitalisation or prolongation of existing hospitalisation, (D) results in persistent or significant disability or incapacity, (E) medical or surgical intervention is required to prevent any of the above, (F) leads to fetal distress, fetal death or consists of a congenital anomaly or birth defect or (G) is otherwise considered medically significant by the investigator. Life-threatening in the definition of an SAE refers to an event in which the subject was at risk of death at the time of the event; it does not refer to an event that hypothetically might have caused death if it were more severe. A planned hospitalisation for a pre-existing condition, without a serious deterioration in health, is not considered to be an SAE.

It is relatively common for this patient group to have SAEs, typically psychiatric hospital admissions, physical health hospital admissions and suicide attempts.

The relationship between gameChange or other research procedure and the occurrence of each SAE will be assessed and categorised. The chief investigator will use clinical judgement to determine the relationship. Alternative causes, such as natural history of the participant’s underlying condition, concomitant therapy, other risk factors, etc, will be considered. The investigator will also consult the current version of the risk analysis report. The chief investigator will make an initial assessment of whether the SAE is potentially related to the device or trial procedures, and the expectedness, and report as necessary to the regulatory authorities within the appropriate timescales (eg, related and unexpected SAEs to the research ethics committee and adverse incidents to the Medicines and Healthcare products Regulatory Agency). The decisions about relatedness and expectedness will be reviewed by the DMEC chair (an independent clinician) in the first instance, and later taken to a DMEC meeting.

We will also record adverse events that are not serious. This would include any adverse device effects from the VR programme, including those resulting from insufficient or inadequate instructions for use, deployment, installation or operation, or any malfunction of the software. It also includes any event resulting from user error or intentional misuse.

### Data management

All trial data will be entered on paper or electronic clinical research forms (CRFs) and transcribed or entered directly into the clinical data management system. The online Red Pill Electronic Data Capture system will be used (https://www.sealedenvelope.com/redpill/). Direct data entry by patients is also possible via Red Pill’s electronic patient-reported outcomes system. Data are pseudonymised using a unique study ID. Personal data and participant identification codes are kept separately from the research data. Access to these data is strictly on a need to know basis. Data are transferred from paper CRFs to the clinical database or recorded directly on eCRFs as soon as possible after a study visit. Validation of all data entered into the clinical database is achieved through manual review. All critical data items will be 100% checked against original source documents, where applicable.

### Analysis

A full statistical analysis plan will be approved before any analysis. We will report data in line with the CONSORT 2018–SPI^16^ and 2025 statements^17^ showing attrition rates and loss to follow-up. All outcome analyses will be conducted by statisticians at Oxford’s Primary Care Clinical Trials Unit. The target estimand is the treatment policy estimand and all primary and secondary analyses will be carried out incorporating data from all participants including those who do not complete treatment. Every effort will be made to follow up all participants in both arms for research assessments.

Treatment effects on primary and secondary outcomes will be estimated using linear mixed effect models fitted to outcome variables at both main follow-up points (8 and 26 weeks). Fixed effects will be site, baseline assessment for the outcome under investigation, treatment, time and time*treatment interactions. Participants will be included as a random intercept to account for repeated measures and nested within therapist to account for clustering by staff deliverer. Treatment effects will be estimated for the primary outcome at each time point and reported separately as adjusted mean differences in scores between the groups with 95% CIs and two-sided p values. We will also calculate an effect size (Cohen’s d), which will be the between group treatment difference divided by the shared SD at baseline.

We will check for differential predictors of missing outcomes by comparing responders to non-responders on key baseline variables. Any significant predictors will be included in the analysis models in a sensitivity analysis. This accounts for missing outcome data under a missing at random assumption, conditional on the covariates included in the model. As a sensitivity analysis, we will assess whether treatment adherence is associated with missing data, and if it is associated, use inverse probability weights or multiple imputation to compare results.

To test the moderation hypotheses, we will extend the analysis model to include as fixed effects the putative moderator and its interaction with treatment; the coefficient of the interaction tests whether there is a differential treatment effect across levels of the moderator variable.

Collection of 34-week data for the control group will provide further information for secondary trial reports on, for example, treatment uptake, satisfaction, acceptability, adverse effects and outcomes.

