**Methods and analysis:**

200 patients with psychosis and severe agoraphobic avoidance will be randomised (1:1) to receive gameChange in addition to treatment as usual (TAU) or to a waitlist control group receiving TAU. Assessments will be conducted blind to group allocation at baseline, 8 weeks (end of treatment) and 26 weeks (follow-up). The trial will be embedded in services in at least seven National Health Service (NHS) trusts across England. The primary outcome is agoraphobic avoidance at 26 weeks assessed with the Oxford Agoraphobic Avoidance Scale. The secondary clinical outcomes are agoraphobic distress, paranoia and social contacts. There will be tests of moderation of the main clinical outcome. Treatment acceptability, adverse effects and cost-effectiveness will also be assessed. The target estimand is the treatment policy estimand and all primary and secondary analyses will be carried out incorporating data from all participants including those who do not complete treatment.

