Two outcome papers have been reported from a randomised controlled clinical trial with 346 patients with psychosis.^3 4^ These show that for any patient with psychosis who has agoraphobia symptoms, there is a significant reduction in fears at the end of treatment. However, a moderation analysis revealed that it was patients with severe agoraphobia and the highest overall mental health symptoms who had the largest gains both post-treatment and 6 months later. It is notable that, 6 months post-treatment, the 6-week gameChange intervention in patients with severe agoraphobia reduced agoraphobia to a large extent (effect size=0.8), reduced paranoia to a moderate extent (effect size=0.4) and improved quality of life to a moderate extent (effect size=0.5). No patient serious adverse events (SAEs) during the trial were linked with gameChange. A peer-led qualitative evaluation reported great enthusiasm for the approach from trial participants.^5^ A paper on satisfaction and side effects showed high satisfaction ratings and low occurrence of side effects that did not affect treatment outcomes or uptake.^6^ And a health economic evaluation^7^ indicated that gameChange may lower costs from an NHS and social care perspective and, by reducing informal caring, from a wider societal perspective too. The analysis also suggested that gameChange may be cost-effective against National Institute for Health and Care Excellence (NICE) thresholds for value per quality-adjusted life-year (QALY) gained.

On the basis of the randomised controlled trial results, gameChange obtained NICE Early Value Assessment (EVA) for medtech approval for use in the NHS: ‘gameChangeVR (a VR technology) can be used in the NHS while more evidence is generated, to treat severe agoraphobic avoidance in people with psychosis aged 16 and over. It should be used with the support of a mental health professional’. The approval is for use for patients diagnosed with psychosis who have severe agoraphobic avoidance (ie, the group that the moderation analysis indicates benefits most). NICE EVA approval is conditional on further evidence generation. The current project is designed to address the evidence gaps identified in the NICE EVA of gameChange.

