### Participants

The principal method of recruitment will be via the relevant clinical teams in the participating mental health services (eg, adult community mental health teams; early intervention services, inpatient units, mental health and well-being hubs, commissioned Voluntary, Community and Social Enterprise (VCSE). Recruitment can also be via research registers, where patients have given consent to be contacted about studies. As this is a real-world evaluation, clinical teams will be encouraged to use the Oxford Agoraphobia Avoidance Scale (O-AS)^8^ as part of routine assessment of patients with psychosis. This would identify people for whom gameChange may well be a suitable fit. It will also be the case that staff deliverers in the clinical teams, or Research Delivery Network research assistants embedded in the clinical teams, would be able to check eligibility against clinical notes.

Informed consent (see online supplemental materials) will be obtained from participants. This will be after provision of the patient information sheet (see online supplemental materials) to the patient, opportunities to ask questions, and at least 24 hours to decide. Our Lived Experience Advisory Panel (LEAP) has also emphasised the importance of patients in participating trusts being able to self-refer to the trial. This will minimise the chances that patients are overlooked by clinical teams or because their clinician was not present at a referral meeting. Hence, we will also advertise the study to patients via posters and leaflets in NHS buildings. However, in all instances, we will seek to confirm that a member of the clinical team gives approval for a patient to enter the trial and to complete the necessary check of eligibility and risk status. Written informed consent will be obtained from all participants.

The inclusion criteria are: participant is willing and able to give informed consent for participation in the trial; aged 16 years or older; attending NHS or commissioned VCSE mental health services; clinical diagnosis of schizophrenia spectrum psychosis or an affective diagnosis with psychotic symptoms; severe agoraphobic avoidance as assessed by the O-AS (score of 6 or above)^8^ and wanting help for that difficulty.

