### Power calculation

The number of participants is based on the means and SDs observed in our original trial. We assume an average cluster size of five participants per therapist and an ICC of 0.01. We calculate power both for the clinical outcome (agoraphobic avoidance) and quality of life.

O-AS-Avoidance: Based on a sample size of 200 and end of treatment means of 3.6 (SD=2.8) in the intervention group and 5.3 (SD=2.2) in the control group, we would have 90% power to detect a difference (5% significance). At 6 months, with means of 3.2 (SD=3.1) in the intervention group and 5.4 (SD=2.1) in the control group, we would have 99% power to detect a difference.

ReQol: Based on a sample size of 200 and end of treatment means of 37.5 (SD=18.7) in the intervention group and 30.6 (SD=13.2) in the control group, we would have 84% power to detect a difference (5% significance). At 6 months, with means of 38.1 (SD=18.0) in the intervention group and 31.3 (SD=12.5) in the control group, we would have 86% power to detect a difference.

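### For the primary outcome, the only patient-level baseline covariate is also the entry variable; adding baseline distress and paranoia could modestly improve precision at almost no cost

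*Protocol article*

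**What the plan says.** The Abstract of the protocol article defines the primary outcome: "The primary outcome is agoraphobic avoidance at 26 weeks assessed with the Oxford Agoraphobic Avoidance Scale". The Analysis section gives the linear mixed model: "Fixed effects will be site, baseline assessment for the outcome under investigation, treatment, time and time*treatment interactions". It adds a random intercept for participant, nested within therapist. Other baseline variables enter in two ways only: as predictors of missing outcomes in a sensitivity analysis, and as putative moderators.

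The Participants section makes the primary outcome's scale an entry criterion: "severe agoraphobic avoidance as assessed by the O-AS (score of 6 or above".

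Distress and paranoia are also measured. The Assessments section begins its list with "The secondary outcomes are: agoraphobic distress (O-AS" and continues with a paranoia scale and social contacts. Assessments take place at 0, 8 and 26 weeks (Trial design and flow chart), and patients are randomised only after the baseline assessment is complete (Randomisation section). The model for each outcome uses that outcome's own baseline, so baseline distress and paranoia will be available for adjustment.

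The Power calculation works from follow-up means and SDs: "At 6 months, with means of 3.2 (SD=3.1) in the intervention group and 5.4 (SD=2.1) in the control group, we would have 99% power".

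**The concern.** Adjusting for baseline narrows the interval to the extent that the baseline predicts the follow-up score. When everyone must score at or above a cut-off on that baseline, its spread shrinks, and so does the share of outcome variance it can explain. The primary outcome is the one outcome whose own baseline is cut directly by eligibility, and apart from site it has no other prognostic term in its model. Baseline distress and paranoia are not cut directly, and they are not used in that model.

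The stake is the width of the interval around the 26-week difference. The trial is meant to inform a NICE guidance update, so the uncertainty of the estimate matters even where power is high. The Strengths and limitations box also describes the trial as powered only for moderate improvements, and if the true effect is nearer that size, precision counts for more. A side benefit is possible: the missing-at-random assumption is conditional on the covariates in the model, and pre-specified prognostic baselines could make it more plausible in the primary analysis itself.

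**Working it through.** **Inputs from the protocol article.** 200 patients randomised 1:1, so 100 per arm. 26-week means 3.2 and 5.4 (difference 2.2), SDs 3.1 and 2.1. Average cluster size 5 and ICC 0.01, so the design effect is 1 + (5 - 1) x 0.01 = 1.04. Two-sided 5% level.

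**Step 1: the plan's own figure.**
- Pooled SD = sqrt((3.1^2 + 2.1^2)/2) = 2.648, so the planned standardised difference is 2.2/2.648 = 0.83.
- SE = sqrt((3.1^2 + 2.1^2)/100) = 0.374 without clustering, and sqrt(0.1402 x 1.04) = 0.382 with it.
- 2.2/0.382 is about 5.76; subtracting 1.96 leaves 3.80, so power is 99.99%. This agrees with the stated 99%. With an assumed 20% loss (80 per arm), SE = 0.427 and power is 99.93%.
- The same method, with no covariates and no dropout, gives 84.0% and 86.1% for ReQoL against the stated 84% and 86%. The stated power therefore appears to take no credit for baseline adjustment. (For O-AS at 8 weeks the method gives 99.7% against a stated 90%. That mismatch is a separate matter and does not bear on this point.)

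**Step 2: how much the truncated baseline explains.** The article gives neither the baseline SD nor the correlation, so two sets of assumed inputs show the range.
- Range restriction: r' = r u / sqrt(1 - r^2 + r^2 u^2), where u is the ratio of restricted to unrestricted SD. With r = 0.5, u = 0.3: r' = 0.15/sqrt(0.7725) = 0.171, so R^2 = 0.029 (unrestricted 0.25). With r = 0.6, u = 0.4: r' = 0.24/sqrt(0.6976) = 0.287, so R^2 = 0.083 (unrestricted 0.36).
- Slope form, with the control follow-up SD of 2.1: R^2 = (b x SD_baseline / 2.1)^2. For baseline SDs of 0.8, 1.0 and 1.5 this is 4%, 6% and 13% at b = 0.5, and 15%, 23% and 51% at b = 1.

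The direction is clear: a narrower baseline explains less. The size is not, since plausible inputs run from about 3% to 51%.

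**Step 3: what extra baselines could add.** Let R^2_add be the share of remaining outcome variance explained by baseline distress and paranoia together (assumed). The SE is multiplied by sqrt(1 - R^2_add). Starting from SE 0.382 and half-width 1.96 x 0.382 = 0.75:

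| R^2_add | SE | SE reduction | 95% CI half-width | Power at difference 2.2 | Power at assumed d = 0.4 |
|---|---|---|---|---|---|
| 0% | 0.382 | 0% | 0.75 | 99.99% | 79% |
| 5% | 0.372 | 2.5% | 0.73 | above 99.99% | 81% |
| 10% | 0.362 | 5% | 0.71 | above 99.99% | 83% |
| 20% | 0.342 | 11% | 0.67 | above 99.99% | 87% |

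Here d is in units of the pooled follow-up SD, so 0.4 is 0.4 x 2.648 = 1.06 points. The starting half-width uses raw follow-up SDs. The planned model already contains baseline avoidance, so its interval should be somewhat narrower than 0.75; the percentage reductions apply either way.

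**The case against.** The strongest reply is that nothing here is wrong. The model adjusts for the stratification factor and the outcome's own baseline, which is conventional and valid. The power calculation borrows nothing from covariates, and at the planned effect no conclusion would change: the half-width moves by at most 0.08 points against a difference of 2.2. All of that stands.

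A second reply is that a full SAP will be approved before analysis and may add covariates. That is possible. But the article does list the fixed effects, and the other roles it gives to baseline variables are in missing-data and moderation analyses, so the suggestion is worth making while the SAP can take it up.

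Third, distress comes from the same instrument as avoidance. If the two are closely related, selection on avoidance restricts distress as well, and distress largely duplicates a term already in the model. This is why the range above starts at zero.

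Three stronger readings are tempting and unsupported. A reader might infer that baseline avoidance explains little and that precision is definitely lost; Step 2 shows that the documents cannot settle this. A reader might convert an added 10-20% into 222-250 equivalent patients (200/0.9 and 200/0.8); that only restates the assumption. And a reader might take the Introduction's statement that "it was patients with severe agoraphobia and the highest overall mental health symptoms who had the largest gains both post-treatment and 6 months later" as evidence that symptom level is prognostic. It reports moderation, that is, who gained most from treatment. A moderator need not explain outcome variance as a main effect, and overall symptoms are neither O-AS distress nor the paranoia score.

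**Conclusion.** This is an optional efficiency improvement, confined to the primary O-AS avoidance analysis; it is not an error in the plan. It is established that the primary model adjusts only for site and own baseline, that eligibility truncates that baseline, and that two further baselines will be collected before randomisation. It is likely, but cannot be quantified from the article, that the truncated baseline explains less than usual. The gain from the added covariates rests wholly on an assumed 0-20% of extra explained variance: between nothing and an 11% smaller standard error, with power at the planned difference above 99% throughout. Power would move noticeably only if the true effect were well below the planned 0.83. The argument does not extend to paranoia or social contacts, whose own baselines eligibility does not cut directly.

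**What to change.** In the Analysis section and the SAP, add baseline O-AS distress and the baseline paranoia score as fixed effects in the primary O-AS avoidance model, alongside site and baseline avoidance, and fix this before any unblinded data are seen. Ideally, first check how much each adds beyond baseline avoidance in the earlier 346-patient trial, restricted to patients scoring 6 or above on the O-AS; if distress adds nothing there, leave it out. That check uses none of this trial's data.

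The cost is one sentence and two degrees of freedom in a trial of 200, with no extra data collection. The downside is small: little or no gain if distress mostly overlaps with avoidance.

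### Both missing-data sensitivity analyses run only if an association with missingness shows up in the trial's own data; one prespecified analysis should always run

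*Protocol article*

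**What the plan says.** All of this is in the protocol article, Methods and analysis, Analysis.

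- **Estimand.** "The target estimand is the treatment policy estimand", and patients who do not complete treatment are included.
- **Primary model.** A linear mixed model of the 8- and 26-week scores, with site, baseline score, treatment, time and time by treatment as fixed effects. Adherence is not in it.
- **First sensitivity analysis.** "We will check for differential predictors of missing outcomes by comparing responders to non-responders on key baseline variables". Then: "Any significant predictors will be included in the analysis models in a sensitivity analysis". The stated basis is: "This accounts for missing outcome data under a missing at random assumption, conditional on the covariates included in the model".
- **Second sensitivity analysis.** "we will assess whether treatment adherence is associated with missing data, and if it is associated, use inverse probability weights or multiple imputation". No test, level or missingness assumption is named for this step.
- **Analysis plan.** "A full statistical analysis plan will be approved before any analysis". It is not shown.

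The article gives no expected attrition, adherence or differential loss.

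**The concern.** Two rules are fixed in the article, and each makes a robustness check depend on an association observed in the same data.

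The first picks covariates by the significance of their link with missingness. That link is only half of what matters: a variable that predicts missingness but not outcome removes no bias. The test is also weak when few outcomes are missing, and a strong prognostic variable can fail it.

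The second concerns adherence, which up to 26 weeks exists only in the gameChange arm. Under a treatment policy estimand non-adherers count in full. If they do worse and are lost more often, the observed gameChange patients over-represent adherers. The mixed model corrects this only as far as site, baseline and any 8-week score carry the information. An imputation or weighting that uses adherence deals with the problem directly, yet it runs only if the association is judged present.

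Both described analyses rest on missing at random (MAR): stated for the first, implied for the second, since weighting and imputation are MAR methods as ordinarily used. The outcome is avoidance of everyday situations, which is a plausible reason for missing an assessment. The trial is meant to inform a NICE guidance update, so readers will want to see how far the 26-week result depends on who was lost.

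**Working it through.** **The plan's own figure.** The article gives no number for missing data. Its Power calculation section sets the scale: 26-week means 3.2 (SD 3.1) and 5.4 (SD 2.1), 200 patients, cluster size 5, ICC 0.01. The difference is 2.2, the pooled SD is sqrt((3.1² + 2.1²)/2) = 2.648, and the design effect is 1 + 4 × 0.01 = 1.04. SE = 2.648 × sqrt(2 × 1.04/100) = 0.382, z = 5.76, and power = Φ(5.76 − 1.96) = 99.99%. This agrees with the stated 99%.

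**Step 1: trigger on baseline covariates.** Assumed: 20% loss (40 missing, 160 observed) and a 5% two-sided test. Power = Φ(d/sqrt(1/40 + 1/160) − 1.96), where the square root is 0.177.

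| Standardised difference | Calculation | Power |
|---|---|---|
| 0.2 | Φ(1.13 − 1.96) | 20% |
| 0.3 | Φ(1.70 − 1.96) | 40% |
| 0.4 | Φ(2.26 − 1.96) | 62% |

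At 10% and 30% loss, a difference of 0.3 gives 25% and 49%. In the other direction, if eight independent variables have no link with missingness, at least one enters with probability 1 − 0.95⁸ = 34%.

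**Step 2: bias if non-adherers are lost more often.** Assumed: 100 in the gameChange arm; adherers gain 2.8 O-AS points and non-adherers 0.4. With 75% adherent the true average is 0.75 × 2.8 + 0.25 × 0.4 = 2.20, the planning difference. With 65% adherent it is 0.65 × 2.8 + 0.35 × 0.4 = 1.96.

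Ignoring the 8-week scores, the observed average at 15% v 35% loss is (63.75 × 2.8 + 16.25 × 0.4)/80 = 2.31. That is an upper limit for this setting, because 8-week scores recover part of the gap. Simulation that uses them (40% of those lost at 26 weeks have an 8-week score, control SDs 2.2 and 2.1, correlation 0.6) gives the fourth column below. The last column is a 5% Fisher test of adherence against missingness, itself an assumption because the article names no test.

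| Adherent; loss in adherers v non-adherers | True | No 8-week scores | MAR without adherence | Trigger opens |
|---|---|---|---|---|
| 75%; 15% v 35% | 2.20 | 2.31 | about 2.3 | about 50% |
| 75%; 12% v 40% | 2.20 | 2.36 | about 2.3 | about 80% |
| 75%; 10% v 50% | 2.20 | 2.43 | 2.37 to 2.38 | about 98% |
| 65%; 10% v 50% | 1.96 | 2.25 | 2.17 to 2.18 | about 99% |

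The excess is therefore about 0.1 in the first two settings and about 0.2 in the last two. Imputation that includes adherence comes within 0.02 of the truth in these settings.

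Over a wider grid (10% to 30% loss, 20% or 30% non-adherent, missingness 1.5 to 3 times as high in non-adherers), the chance that a 5% test opens this trigger runs from about 11% to 96%.

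**Step 3: departures from MAR.** Assumed: 20% loss per arm and missing gameChange outcomes worse by delta. SE = sqrt(3.1² × 1.04/80 + 2.1²/80) = 0.424, and z = (effect − 0.2 × delta)/0.424.

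| Observed effect | delta 0 | delta 1 | delta 2 | Delta at which z = 1.96 |
|---|---|---|---|---|
| 2.2 | 5.18 | 4.71 | 4.24 | (2.2 − 0.832)/0.2 = 6.8 |
| 1.1 | 2.59 | 2.12 | 1.65 | (1.1 − 0.832)/0.2 = 1.3 |

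A separate simulation used a true effect of −1.0 and outcome-dependent loss in the gameChange arm. The observed-data estimate moved to about −1.25 and −1.46. The baseline trigger opened in about 28% of runs, as it did without such loss, and the added variables moved the estimate by about 0.00 (SD 0.03). Those extra variables were unrelated to outcome by construction. The result shows that chance entries are close to harmless and that the trigger is no signal of this kind of loss.

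**The case against.** Several counter-arguments stand.

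- **The checks may well run.** A reader might infer that they will usually stay switched off. The documents do not support that: no attrition or adherence figure is given, and in the settings above with the largest bias the adherence trigger opens in about 98% to 99% of trials. It is missed about half the time only where the bias is near 0.1.
- **Significance testing is stated for the first analysis only.** The second says "if it is associated, use inverse probability weights or multiple imputation to compare results" and names no test. It is data-dependent, but the Fisher test above is my stand-in.
- **The described analyses can move the result.** It would be too strong to say that they cannot challenge the treatment-policy estimate. When the adherence analysis runs, it recovers almost all of the bias in step 2. What neither analysis can challenge is MAR itself.
- **The analysis plan may fill gaps.** The list of key baseline variables, the choice between weighting and imputation, and any analysis outside MAR are commonly settled there. Their absence from an article is no error, and the article does not say that these are its only sensitivity analyses.
- **The bias is small and conditional.** An excess of 0.1 to 0.2 is about a quarter to a half of the 0.42 standard error. Loss driven by avoidance already recorded at baseline or 8 weeks is handled by the mixed model. At the planning effect the result is robust; a reversal needs about half that effect and a penalty applied to gameChange alone. The step 3 standard error also ignores the gain from baseline and 8-week scores.

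None of this defends the two triggers themselves, which the article states and which have no advantage over running the analyses unconditionally.

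**Conclusion.** The point holds as a criticism of two stated rules. Making the sensitivity analyses conditional on observed associations is a poor choice. The first rule selects on the wrong criterion and misses moderate predictors (about 40% power at a difference of 0.3 with 20% loss). The second can leave a modest lean towards gameChange of about 0.1 O-AS points unexamined in up to about half of trials when differential loss is moderate; where the lean is nearer 0.2, the check would rarely be missed.

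These sizes rest wholly on assumed attrition, adherence and outcome gaps between adherers and non-adherers. The documents do not show that the primary estimate is biased, only the direction it would take if non-adherers do worse and are lost more often. The primary model is not faulted. This is a cheap improvement and not a threat to the trial's main conclusion at the planned effect; it would matter more if the observed effect were about half the planned 2.2 points.

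**What to change.** Remove both triggers from the Analysis section and carry the change into the statistical analysis plan before it is approved.

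1. Always run one prespecified sensitivity analysis of the 26-week O-AS avoidance score: multiple imputation within arm, using site, baseline and 8-week O-AS, a fixed list of baseline variables already collected (for example age, gender, diagnosis, paranoia and ReQoL) and, in the gameChange arm, sessions attended. Analyse the imputed data with the primary model.
2. On the same imputations, add a delta-adjusted analysis, for example 0 to 3 O-AS points worse for imputed gameChange values, and report the tipping point.
3. Keep the comparison of patients with and without outcomes as description only.

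The cost is a change of wording and a little more analysis work. No new data are needed and the primary model is unchanged. The one downside is a sensitivity result that may look slightly less favourable to gameChange.
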